## Abstract

**Background:**

There are many studies that associate vitamin D serum levels in older persons with muscle strength, physical performance and risk of fractures and falls. However, current evidence is insufficient to make a general recommendation for administrating calcium and vitamin D to older persons. The objective of this study is to determine the effectiveness of calcium and vitamin D supplementation in improving musculoskeletal function and decreasing the number of falls in person aged over 65 years.

**Methods/Design:**

Phase III, randomized, double blind, placebo-controlled trial to evaluate the efficacy of already marketed drugs in a new indication. It will be performed at Primary Care doctor visits at several Healthcare Centers in different Spanish Health Areas. A total of 704 non-institutionalized subjects aged 65 years or older will be studied (sample size calculated for a statistical power of 80%, alpha error 0.05, annual incidence of falls 30% and expected reduction of 30% to 20% and expected loss to follow up of 20%). The test drug containing 800 IU of vitamin D and 1000 mg of calcium will be administered daily. The control group will receive a placebo. The subjects will be followed up over two years. The primary variable will be the incidence of spontaneous falls. The secondary variables will include: consequences of the falls (fractures, need for hospitalization), change in calcidiol plasma levels and other analytical determinations (transaminases, PTH, calcium/phosphorous, albumin, creatinine, etc.), change in bone mass by densitometry, change in muscle strength in the dominant hand and change in musculoskeletal strength, risk factors for falls, treatment compliance, adverse effects and socio-demographic data.

**Discussion:**

The following principles have been considered in the development of this Project: the product data are sufficient to ensure that the risks assumed by the study participants are acceptable, the study objectives will probably provide further knowledge on the problem studied and the available information justifies the performance of the study and its possible risk for the participants.

If calcium and vitamin D supplementation is effective in the prevention of falls and fractures in the elderly population, a recommendation may be issued with the aim of preventing some of the consequences of falls that affect quality of life and the ensuing personal, health and social costs.

**Trial Registration:**

ClinicalTrials.gov:  NCT01452243

Clinical trial authorized by the Spanish Medicines Agency: EudraCT number 2006-001643-63.

## Background

Vitamin D insufficiency is common in older people [1] and is associated with several disorders related to aging such as osteoporosis, which leads to a significantly increased risk of bone fractures [2]. These are associated with physical disabilities, reduced quality of life, increased mortality and increase in healthcare costs [3]. According to the SENECA study [4], carried out in elderly people in 11 European countries, 47% of the elderly people had vitamin D deficiency (< 12 ng/ml). This deficiency was more common in Mediterranean countries than in Northern European countries, probably because in the latter countries there is a greater consumption of fish, fortified foods and vitamin D supplements.

According to several authors [5-10], vitamin D serum level is related to muscular strength, physical functional status and risk of fractures and falls, the annual incidence of which is around 30% in persons over 65 years [11]. It has been demonstrated that in institutionalized women, daily calcium and vitamin D supplementation decreases the number of falls and risk of fracture, increases bone mineral density and improves musculoskeletal function [12-14]. The conclusion in a Cochrane review [15], designed to determine the effect of vitamin D on the prevention of fractures in elderly people with senile or post-menopausal osteoporosis, is that the efficacy of this vitamin or of its analogues in the prevention of fractures remains unknown. A reduction in hip fractures in institutionalized, frail, elderly people was observed with the concomitant administration of calcium supplements, but the effect in community-dwelling, younger, healthy older adults was unknown.

According to the result of another systematic review, there is a balance between positive and neutral results [16]. Its use is controversial as it seems clear that is has a positive effect on sub-clinical vitamin D deficiency, resolving a sub-clinical hypovitaminosis state or osteomalacia, but for people living at home not all studies show beneficial effects on bone mass [17]. In their conclusions, the authors of this review state that, overall the evidence analyzed is of intermediate consistency, sufficient for its individualized use, especially in patients with calcium or vitamin D deficiency. However, in order to be able to issue a generalized recommendation, rigorously designed clinical trials are needed, with a sufficient sample size, which can be reproduced in different clinical populations and geographical areas.

Another systematic review [18], aimed at evaluating the effect of vitamin D on strength, physical performance and falls in elderly people in 13 clinical trials (2496 patients), concluded that although there is insufficient evidence that vitamin D supplementation improves physical function in the elderly, some data suggest a benefit of vitamin D combined with calcium. Large, well-designed studies are needed to confirm these findings.

More recently [19], in a meta-analysis performed with a sample of 1237 patients, it was concluded that vitamin D supplementation appears to reduce the risk of falls by more than 20%, both in institutionalized and ambulatory elderly people, although further studies should be considered on the effects of different types and doses of vitamin D and the role of calcium supplements.

There is now general agreement on the importance of vitamin D deficiency in the pathogenesis of osteoporosis and the loss of muscle strength in elderly subjects. However questions are raised on how supplements should be used for prevention in the future. Studies have been performed in different populations with different baseline vitamin D status and different administration regimens, which makes it difficult to compare results [20]. According to forecasts, the population of over 65 years in developed countries will have doubled by 2050, therefore, this will be the age group with the greatest risk of developing osteoporosis and related fractures [21].

Calcium and vitamin D are the mainstay in the treatment of osteoporosis and it is accepted [22] that for women over 65 years with a bone mineral density of -2.5, supplementation (1200 mg of calcium and 800 U of vitamin D) is justified. These can be taken together with other drugs, depending on the presence of risk factors for fracture, the choice of which should be individualized.

Perhaps healthcare policies need to be adopted on the administration of vitamin D supplements in populations at risk of osteoporosis, such as the elderly population and post-menopausal women in Spain and other Mediterranean countries [20]. Vitamin D supplementation could be an attractive public health intervention measure; although further studies are needed before a generalized recommendation can be issued in this respect.

### Study objectives

The first objective is to determine the efficacy of calcium and vitamin D supplementation at doses of 1200 mg and 800 IU, respectively, to reduce the incidence of falls and fractures in non-institutionalized elderly people.

The second objective is to measure and compare treatment groups (calcium and vitamin D vs placebo) as regards muscle strength and musculoskeletal function, bone mineral density, calcidiol level and treatment safety.

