### Definitions of the primary variables and measuring methods

The primary variable will be the incidence of spontaneous falls according to the FICSIT (Frailty and Injury: Cooperative Study of Intervention Techniques) definition: "Unintentionally coming to rest on the ground, floor, or other lower level. Coming to rest against furniture or a wall was not counted as a fall." Information on the circumstances of the fall (apparent cause, activity performed, time and place and need of help) will be obtained by an interview.

The following are the secondary variables:

- Consequence of falls (bone fractures at any location, need for healthcare, need for hospitalization, bed-ridden).

- Change in calcidiol [25(OH)D3] plasma levels (determined by RIA at baseline and at 6 and 18 months). Vitamin D deficiency is defined as a calcidiol plasma level lower than 10 ng/ml.

- Levels of transaminases, parathyroid hormone (PTH), calcium, phosphorous and serum creatinine, determined by tests on venous blood samples obtained in a fasted state. Calcium/creatinine index, determined by analysis of second morning urine.

- Change in bone mass (bone density or mineral content) obtained by densitometry (risk of fracture). Osteoporosis will be diagnosed based on a densitometry T-score of less than 2.5 in the vertebral column, according to WHO criteria.

- Change in muscle strength in the dominant hand. Determined by dyanometry (with a mean of 3 attempts to obtain a muscle strength measurement).

- Changes in musculoskeletal function, determined by the timed up and go test (the elderly person gets up from a chair with arms, walks three meters, turns round, walks back and sits down again). Taking more than 20 seconds indicates a high risk for falls.

- Stratification and potentially confounding variables; gender, age and other demographic data (social class, education level, marital status).

- Risk factors for falls: taking pre-disposing medication, health problems, toxic habits, physical exercise, living arrangements, sight or hearing difficulties, functional status (Katz index).

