### Statistical analysis

After performing data cleaning and imputation, exploratory analysis and categorization or transformation of variables the following analyses will be performed:

- Comparison of the variables of interest and the stratification and potentially confounding variables in the treated and non treated groups at the start of the study. We will determine if, despite using randomized assignment, the two groups are homogenous.

- A first raw analysis will be performed to calculate the following parameters and their confidence intervals: ARR (absolute risk reduction), RRR (relative risk reduction) and NNT (number necessary to treat). A stratified analysis will also be performed adjusting for each independent variable. If there are differences between the raw RR and the adjusted RR, the homogeneity between the categories will be determined to establish if the variable is effect modifying or confounding. The incidence of the variables in each group will be described and compared (comparison of proportions by the chi-squared test).

- A survival (fall-free period) analysis will be performed in both study groups (Kaplan-Meier and Log Rank test). Then the effect of treatment on the risk of falls will be determined by constructing a Cox proportional hazards model.

- The effect of treatment on calcium and vitamin D levels will be estimated adjusted for changes in treatment compliance (generalized linear models for repeated measures).

Data will be analyzed on an intention to treat basis including all randomized patients in the efficacy and safety analyses according to their randomized treatment group regardless of the treatment received. A per protocol analysis will also be performed for the primary variables. This will exclude patients who did not meet any of the selection criteria and did not comply with treatment.

For ethical reasons an intermediate analysis will be performed to decide if the study should be discontinued prematurely because of frequent adverse effects occur or an obvious improvement in the test group.

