## Discussion

If calcium and vitamin D supplementation is effective in the prevention of falls and fractures in the elderly population, a recommendation may be issued with the aim of preventing some of the consequences of falls that affect quality of life and the ensuing personal, health and social costs.

Using a randomization procedure will reduce selection bias as the investigator does not assign the treatment and any factor affecting participation will be equally divided between the two groups. Confounding is also reduced because randomization tends to share the determining factors that may affect the final result equally among the groups.

However, bias in the collection of information could occur in the study, such as patient evolution, determined by the aging process throughout the two study years, also the regression toward the mean or tendency of the continuous variables to approach the mean value in successive measurements. In our case this is applicable to the number of falls by the elderly people or the analytical test results. Furthermore, the participants, who are aware of the study objectives, could contribute to what is termed "hypothesis guessing" and try to downplay the importance of falls without consequences. There will also be a possible risk of differential loss to follow up between the groups being compared, due to the duration of the study and the placebo effect, which could contribute to patients abandoning the study because they consider the medication they are given is having no effect.

Follow-up visits with controls every 3 months will allow us to balance recommendations on treatment compliance and increase the possibility of detecting adverse effects. This will give us greater control over the development of the study.

As regards problems of external validity, the participants may not represent all eligible subjects if the rate of non responders were high. Furthermore, the study population characteristics (socio-economic level, life-style, etc.) may mean that the results cannot be directly transferred to any other population.

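### Fractures stand in the first objective although only falls are primary and sized, and the falls ARR, RRR and NNT come from crude two-year proportions that depend on how losses are counted

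*Protocol article*

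**What the plan says.** **Objective and endpoint.** In the Protocol article, the Study objectives section states that the first objective is "to reduce the incidence of falls and fractures in non-institutionalized elderly people". The section defining the variables says "The primary variable will be the incidence of spontaneous falls", and its list of secondary variables opens with "Consequence of falls (bone fractures at any location". The abstract ranks them the same way: falls primary, fractures among the secondary variables. The Sample size section works only with falls, 30% against 20%. The Discussion links a possible recommendation to preventing both falls and fractures.

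**Falls analysis.** The Statistical analysis section says "A first raw analysis will be performed to calculate the following parameters and their confidence intervals", the parameters being ARR, RRR and NNT. It compares incidences through "comparison of proportions by the chi-squared test". Kaplan-Meier curves with a log-rank test follow, then a Cox model. The same section places data cleaning and imputation before all analyses, without describing the imputation, and applies intention to treat to everyone randomized.

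**Loss.** Follow-up is two years and the Sample size section allows for 20% loss. The Discussion adds: "There will also be a possible risk of differential loss to follow up between the groups being compared".

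**The concern.** Two things do not fit together.

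1. The objective that a reader takes as confirmatory names two outcomes, while the endpoint hierarchy and the sample size support one. A fracture result could be presented as answering the first objective although the trial was not sized for it. A null fracture result could equally be read as evidence of no effect.

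2. The ARR and NNT are the figures that a recommendation would quote. A crude two-year proportion needs a decision on participants who leave before 24 months without a fall. Counting them as non-fallers and leaving them out give different answers, and neither equals the two-year risk. The plan already produces an estimate that uses partial follow-up (Kaplan-Meier), but does not take the ARR, RRR and NNT from it.

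**Working it through.** **The plan's own figure.** Inputs from the Sample size section: 30% against 20%, alpha 0.05 (taken as two-sided), power 80%. With pooled variance under the null,

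n = [1.96·√(2·0.25·0.75) + 0.8416·√(0.30·0.70 + 0.20·0.80)]² / 0.10² = (1.200 + 0.512)² / 0.01 ≈ 293 per arm.

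This agrees with the stated 293 per arm, 586 in all. It is a falls calculation only. Of the 704 to be selected, 20% loss leaves 704 × 0.8 = 563.2, or 281.6 per arm.

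**Power for fractures.** The control risk p₁ is an assumption, and p₂ = ⅔·p₁ is the falls effect carried over. With p̄ the mean of the two,

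power = Φ{[(p₁ − p₂)·√n − 1.96·√(2p̄(1 − p̄))] / √(p₁(1 − p₁) + p₂(1 − p₂))}, n = 281.6.

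For 3% against 2%: (0.1678 − 0.4327) / 0.2207 = −1.20, so power is 11.5%.

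| Assumed 24-month control risk | Active | Power |
|---|---|---|
| 3% | 2% | 11.5% |
| 5% | 3.3% | 16.6% |
| 8% | 5.3% | 24.4% |

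Widening the range to 2% to 10% at 293 per arm gives 9% to 31%. Power of 80% would need 5,788 down to 1,079 per arm.

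**Crude falls proportions.** The abstract gives 30% as an annual incidence. Assume constant hazards matching 30% and 20% a year: λ = −ln 0.7 = 0.3567 and −ln 0.8 = 0.2231. The true 24-month risks are 1 − 0.7² = 51% and 1 − 0.8² = 36%, so ARR is 15.0 points and NNT 1/0.15 = 6.7.

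Let a proportion L be lost by 24 months at constant hazard μ = −ln(1 − L)/2, independently of falls, with no effective imputation. Then:

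- completed without a fall: S = exp(−2(λ + μ))
- observed to fall: F = λ/(λ + μ) · (1 − S)
- crude risk with the lost counted as non-fallers: F
- crude risk among known outcomes: F/(F + S)

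*Equal 20% loss.* Control F = 0.4631, S = 0.392. Active F = 0.3253, S = 0.512.
- Lost as non-fallers: 0.4631 − 0.3253 = 13.8 points (NNT 7.3).
- Known outcomes: 0.5416 − 0.3885 = 15.3 points (NNT 6.5).
- With no true effect, both differences are zero.

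*Assumed 25% placebo, 15% active.* Control F = 0.4507, S = 0.3675. Active F = 0.3343, S = 0.544.
- Lost as non-fallers: 11.6 points (NNT 8.6).
- Known outcomes: 0.5509 − 0.3806 = 17.0 points (NNT 5.9).
- No true effect (active F = 0.4752, S = 0.4165): 0.4507 − 0.4752 = −2.5 points, or 0.5509 − 0.5329 = +1.8 points.

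Simulation under the same unequal-loss assumptions agrees to within 0.1 point (11.7, 17.1, −2.4, +1.8). At 352 per arm with no true effect and the lost counted as non-fallers, chi-squared rejects 10.3% of the time at nominal 5%, and log-rank 4.9%. Under equal 20% loss they reject 5.2% and 4.8%.

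**The case against.** **Fractures.** The endpoint hierarchy is clear: the abstract and the definitions section both name one primary variable, so no primary fracture analysis is planned. That stands, and it makes this a mismatch of wording rather than a wrongly specified primary endpoint. The objective still says something else, and the power range rests on an assumed fracture risk.

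**Loss.** A reader might infer that the analysis ignores the 20% loss. The documents do not support that. Loss is allowed for in the sample size, imputation comes before the analyses, and intention to treat covers all randomized participants. The imputation method may sit in a fuller document. The word raw is set against adjusted in the same section, so it means crude, not complete-case.

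A reader might also infer that the protocol expects losses to differ by arm. It calls this a possible risk, and the 25%/15% split used above is an assumption. Equal loss gives no bias under the null and shifts the ARR by about a point or less.

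**Several tests.** A reader might infer that chi-squared, log-rank and Cox are three separate chances of success, which if independent would give 14.3% type I error. Log-rank and unadjusted Cox are nearly one test. In simulation with equal 20% loss, rejection by either chi-squared or log-rank occurs 6.5% of the time. Naming the deciding test is also commonly left to the analysis plan.

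**Number of falls.** The abstract's aim of "improving musculoskeletal function and decreasing the number of falls" might suggest that a model for repeated falls is missing. The Study objectives, Sample size and definitions sections all speak of incidence, so this is looser abstract wording.

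**Kaplan-Meier.** It is unbiased only if loss is non-informative. The Discussion describes people leaving because they see no effect, and death and immobilizing illness are listed among the reasons for discontinuation. This objection stands as a limit on the fix.

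**Conclusion.** The concern holds in a limited form.

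- **Objective.** The first objective is wider than the primary variable and the sample size. At an assumed control fracture risk of 3% to 8% and a one-third reduction, power is about 11% to 24%, so the trial cannot carry a first-objective fracture claim.
- **Falls estimates.** Without effective imputation, the crude ARR depends on the counting rule. Against a true 15.0 points it is 13.8 or 15.3 under equal 20% loss, and 11.6 or 17.0 under the assumed 25%/15% loss, with about −2.5 or +1.8 points under the null. These figures rest on constant hazards, on the 30% and 20% annual risks holding for both years, and on loss independent of falls. A sound imputation would reduce the errors.

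The documents do not support the broader claims that the planned loss is disregarded, that unequal loss is anticipated as a fact, or that multiple falls tests seriously inflate error. Both remaining points merit correction because the changes are small and the figures concerned would inform a recommendation.

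**What to change.** 1. Restrict the first objective to falls and list fractures with the secondary outcomes, matching the definitions section and the abstract.
2. Derive ARR, RRR and NNT, with confidence intervals, from the 24-month Kaplan-Meier risks by intention to treat. Keep the crude proportions as a sensitivity analysis, stating how participants lost without a fall are counted.
3. Treat the log-rank and Cox analysis already planned as the one that decides the falls question.

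**Cost.** Only wording and analysis text change. Kaplan-Meier curves are already planned, so no new data are needed. The sponsor gives up a first-objective fracture claim. The Kaplan-Meier risks still assume non-informative loss, so reasons for loss should be reported by arm. The sample size was based on comparing proportions, so the deciding analysis would differ from the sizing basis, and the protocol should say so. Under the hazards assumed above with equal 20% loss and 352 per arm, simulated power is 97% for log-rank and 96% for chi-squared, so the change of test should not cost power.

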## Methods/design

### Design

Phase III clinical trial to evaluate the efficacy and safety of already marketed drugs in a new indication. Parallel group, randomized, double blind, placebo controlled trial.

### Study location and subjects

Patients will be recruited at primary care doctor visits. The subsequent visits will be at the health Centers of the participating Spanish autonomous communities: Castille-La Mancha, Andalusia, the Balearic Islands and Catalonia.

The target population is non-institutionalized patients of 65 years or over. The inclusion criteria are: aged over 65 years with normal renal function, normal transaminase levels, normal calcium blood levels, not homebound (not immobilized) nor in socio-healthcare institutions. The exclusion criteria are: need for medical treatment with calcium or vitamin D, hypersensitivity to or contraindication for calcium or vitamin D, medical treatment that includes calcium or vitamin D, physical disability that impedes their collaboration, taking thiazide diuretics, oral anticoagulants, hormone replacement therapy, digitalis drugs, anticonvulsants or barbiturates and having any of the following diseases: lithiasis, renal impairment (serum creatinine > 1.4 mg/dl), hypo or hyperthyroidism, Paget's disease, chronic liver disease, tumors, sarcoidosis, impaired intestinal absorption or chronic alcoholism (> 40 g/day).

